## Methods and analysis

### Trial design and setting

OPERA is a double-blinded, superiority, randomised, placebo-controlled, multi-centre clinical trial of an investigational medicinal product (CTIMP). This is a multicentre trial in England, which will be undertaken in specialist clinics in secondary/tertiary referral centres (or as per local set up). These centres will be specialists in the area of PBC management and will manage patients from across their local region. To improve trial efficiency, we will also use an innovative augmented binary analysis method^25^ to improve the precision of a trial where a dichotomous endpoint is derived from continuous data. Using this method substantially reduces the sample size needed for a power of 90%.

The trial population will be newly diagnosed, non-cirrhotic PBC patients, with less than 3 months treatment with UDCA at the time of consent and at an enhanced risk of not achieving biochemical disease remission (based on URS) with UDCA first-line therapy alone. Potentially eligible participants will be invited for a screening visit where informed consent will be received (online supplemental material). Patients will be encouraged to ask questions and will be informed of their right to withdraw from the trial. Potential participants will have sufficient time to review the trial documentation prior to this screening visit. Consent for the optional biopsy sub-study will be through an optional clause on the main trial informed consent form. The trial comprises a 26-week treatment phase in a cohort of 106 participants (OCA n=53; placebo n=53), followed by a 26-week follow-up period. All participants will continue to receive standard of care background treatment with UDCA throughout the trial.

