### Objectives and outcomes

The primary and secondary objectives for the trial are described in table 1.

**Table 1 T1:** Objectives and outcome measures

Objectives	Outcome measures
Primary	
To assess the impact of first-line obeticholic acid therapy combined with UDCA, compared with placebo combined with UDCA, in achieving biochemical remission of disease in new onset PBC patients with an enhanced disease risk.	Percentage of participants showing normalisation of serum alkaline phosphatase and total bilirubin levels at 26 weeks (visit 5)—defined as biochemical remission.
Secondary	
(a) To assess whether biochemical remission is sustained following discontinuation of experimental therapy and reversion to UDCA standard of care therapy.	(a) Percentage of participants in each arm showing sustained normalisation of serum alkaline phosphatase and total bilirubin levels at 52 weeks (visit 6).
(b) To assess the degree of biochemical improvement with obeticholic acid therapy combined with UDCA standard of care therapy compared with placebo.	(b) Magnitude of alkaline phosphatase and bilirubin reduction from baseline to 26 weeks (visit 5), assessed as a continuous variable.
(c) To assess impact of obeticholic acid therapy combined with UDCA standard of care therapy compared with placebo using conventional therapy response criteria (as used in current clinical practice).	(c) Percentage of participants attaining serum alkaline phosphatase values lower than 1.67× the upper limit of normal and a bilirubin <1× the upper limit of normal at 26 weeks (visit 5). These are termed the POISE criteria and are widely applied as outcome measures in conventional clinical trials of second-line PBC therapy. Change in liver stiffness assessed by Transient Elastography (FibroScan) from screening to week 26.
(d) To assess the safety and tolerability of obeticholic acid as first line therapy in PBC.	(d) AE and SAE Reporting up to 26 weeks (visit 5).
(e) To assess the impact of the intervention compared with placebo on symptom severity and participant quality of life.	(e) PBC-40 (change from baseline to 26 weeks (visit 5) and 52 weeks (visit 6)). (f) EQ-5D-5L (change from baseline to 26 weeks (visit 5) and 52 weeks (visit 6)). (g) Patient Health Questionnaire (26 and 52 weeks).
Experimental	

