### Intervention

From baseline, participants will receive 5 mg once a day of OCA or placebo to be taken orally for 12 weeks. OCA or placebo will then be titrated up to 10 mg once a day from visit 4 (week 12±1 week) until visit 5 (week 26±1) according to tolerability. The participants in the OPERA trial will receive UDCA in combination with the trial IMP (OCA or matched placebo). UDCA will be prescribed in line with NHS Standard of Care (usually 13–15 mg/kg daily) and will be prescribed, dispensed and received by the participant, outside of the parameters of this trial. Intolerability to UDCA will be managed as per standard of care. Treatment with UDCA will be recorded as a concomitant medicine.

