### Pharmacovigilance

All adverse events (AEs) occurring from consent to the end of trial participation will be recorded in the CDMS as well as the participant’s medical notes (with the exception of protocol specific reporting exclusions). AEs will be MedDRA coded; MedDRA, the Medical Dictionary for Regulatory Activities terminology, is the international medical terminology developed under the auspices of the International Council for Harmonisation of Technical Requirements for Pharmaceuticals for Human Use (ICH). MedDRA trademark is registered by ICH.

AEs meeting the seriousness criteria (serious AEs (SAEs)) will be reported within 24 hours of awareness. A SAE for the OPERA trial is any untoward medical occurrence that:

Results in deathIs life-threatening*Requires inpatient hospitalisation or prolongation of existing hospitalisationResults in persistent or significant disability/incapacityConsists of a congenital anomaly or birth defectOther important medical events that jeopardise the participant or require intervention to prevent one of the above consequences

*Life-threatening refers to an event in which the participant was at immediate risk of death at the time of the event; it does not refer to an event which hypothetically might have caused death if it were more severe. The assessment of expectedness will be performed by the CI against the approved Reference Safety Information (RSI) for the trial (SmPC for OCALIVA 5 mg, section 4.8 - Undesirable Effects). Suspected Unexpected Serious Adverse Reactions (SUSARs) will be reported to the MHRA (Medicines and Healthcare products Regulatory Agency) and REC (Research Ethics Committee) within the required regulatory reporting timelines.

In the event of a trial participant or their partner becoming pregnant during their participation in the trial, this will be reported within 24 hours of awareness.

Emergency unblinding is available via the 24-hour web-based randomisation system for valid medical or safety reasons.

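### The only stated safety outcome closes at visit 5, when dosing ends, so adverse events recorded after the last dose of treatment completers fall outside the defined between-arm comparison

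*Protocol article*

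**What the plan says.** Table 1 (Objectives and outcomes) gives objective (d) as "To assess the safety and tolerability of obeticholic acid as first line therapy in PBC". The matching outcome is "AE and SAE Reporting up to 26 weeks (visit 5"). No other safety outcome appears in the article.

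The Intervention section has trial medication "titrated up to 10 mg once a day from visit 4 (week 12±1 week) until visit 5 (week 26±1"), so a participant who completes treatment stops at the visit that closes the safety outcome. Trial design and setting describes a 26-week treatment phase "followed by a 26-week follow-up period".

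The Pharmacovigilance section sets a wider recording window: "All adverse events (AEs) occurring from consent to the end of trial participation will be recorded in the CDMS". It allows for protocol-specific exclusions, which the article does not list. The Analysis section defines the safety population by receipt of at least one dose and gives it no time window.

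Other outcomes in Table 1 run past visit 5. Secondary (a) is "sustained normalisation of serum alkaline phosphatase and total bilirubin levels at 52 weeks (visit 6"), and PBC-40, EQ-5D-5L and the Patient Health Questionnaire are also assessed at 52 weeks.

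**The concern.** For treatment completers the safety outcome ends on the last day of dosing. An event caused by the drug but appearing or diagnosed shortly after the last tablet is recorded, yet it does not count in the outcome by which the arms are compared. The same holds for anything in the following 26 weeks.

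This matters because stopping the trial drug at week 26 is part of the design: the trial asks whether benefit persists after it is stopped and follows remission and quality of life to week 52. As worded, the defined outcomes follow benefit through the off-drug period but adverse events only to its start. The window is a stated rule, so an analysis plan that follows Table 1 would inherit the cut at visit 5.

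**Working it through.** The plan gives no figure to reproduce on this point. The check sets the windows side by side.

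| Item | Section | Start | End |
|---|---|---|---|
| Trial medication | Intervention | baseline | visit 5 (week 26±1) |
| Safety outcome (d) | Table 1 | not stated | visit 5 (26 weeks) |
| Adverse event recording | Pharmacovigilance | consent | end of trial participation |
| Remission and quality of life | Table 1 | baseline | visit 6 (52 weeks) |

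**Length of the excluded period.** Treatment 26 weeks + follow-up 26 weeks = 52 weeks. That recording continues to week 52 is an inference: Pharmacovigilance says end of participation, and the follow-up ends at visit 6. The share of planned time outside the outcome is 26 / 52 = 50%. With 106 participants this is 106 × 26/52 = 53 person-years, or 26.5 per arm of 53. If 96 are followed (the 48 per group on which the trial is powered), it is 96 × 26/52 = 48 person-years. These figures describe observation time and say nothing about event rates.

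**Lag after the last dose.** For completers, end of outcome minus end of dosing = visit 5 − visit 5 = 0. For a participant who stops early, say at week *s* < 26, the outcome still covers 26 − *s* weeks off drug, because the Discontinuation and withdrawal section invites such participants to complete all visits. The absence of a lag therefore affects completers, and late discontinuers in part.

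**Possible confounding in the later period.** The Introduction says that participants who relapse are assessed for OCA one year after starting UDCA. Eligibility allows up to about 3 months (13 weeks) of UDCA before consent. The earliest such point is 52 − 13 = about week 39 after consent, which precedes visit 6. Under that rule, the first part of the follow-up (to about week 39 after consent) should be free of open OCA. The rest may include it in either arm.

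**The case against.** The strongest defence is that recording more than a named outcome uses is ordinary practice. Objective (d) concerns OCA as first-line therapy, and a window equal to the treatment phase fits it. Later events are still recorded and MedDRA coded, serious ones are reported within 24 hours, and a Data Monitoring Committee oversees the trial. Nothing prevents the analysis plan from tabulating later events by arm. Ending at visit 5 also avoids the period in which open OCA may start.

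Much of this stands, and it rules out several stronger readings that a reader might infer:

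- *That Table 1 contradicts Pharmacovigilance.* It does not. One section sets what is recorded, the other what one outcome counts.
- *That the trial is blind to later harm.* The document does not support this. The loss is from the defined comparison, while data collection and safety monitoring continue.
- *That all off-drug time is excluded.* Early discontinuers' time up to week 26 is included.
- *That harm from withdrawal is one of the trial's questions.* No objective names it. The stated questions after week 26 concern remission, relapse prediction, symptoms and quality of life.
- *That a known share of events is missed.* If events lagged by 2 to 4 weeks and were triggered evenly over dosing, 2/26 = 8% to 4/26 = 15% of those lagged events would be missed in completers. The lag and the even spread are assumptions with no source in the document.
- *That the unstated start of the window is a fault.* Handling of events before the first dose is ordinary analysis-plan detail.

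The defence does not explain why the stated outcome allows completers no time after the last dose, or why data already being collected are left out of it. Confounding late in follow-up is a reason to report that period separately; it does not justify closing the outcome at the last dose.

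**Conclusion.** The concern holds in limited form. Secondary outcome (d) stops at visit 5, which for treatment completers means no lag after the last dose and no follow-up period in the only stated between-arm safety outcome. Half of the planned 52 weeks lies outside it, assuming that end of trial participation means visit 6. The number of events lost cannot be estimated, because the document gives no event rates or lag times. The primary analysis, the sample size and data collection are unaffected. This is an inexpensive improvement to how one secondary outcome is defined; it does not undermine the trial's main conclusion.

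**What to change.** Reword outcome (d) so that adverse events and serious adverse events in the safety population are summarised by arm in two separate windows:

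1. On treatment: the dosing period plus a lag after each participant's own last dose. The trial team should fix and justify the lag length before any unblinded data are seen.
2. After treatment: from the end of that lag to visit 6, described separately, with any second-line therapy (including open OCA) flagged by arm and start date.

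The windows should not be pooled into a single comparison to week 52, since the later one may no longer contrast OCA with placebo. No new data are needed, because events are already recorded to the end of participation. The cost is a change of outcome wording, one extra set of tables and a later window that may be partly confounded by second-line therapy. The Analysis section says the analysis plan is finalised before the trial statisticians receive unblinded data, so the change should be made by then.

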### Intervention

From baseline, participants will receive 5 mg once a day of OCA or placebo to be taken orally for 12 weeks. OCA or placebo will then be titrated up to 10 mg once a day from visit 4 (week 12±1 week) until visit 5 (week 26±1) according to tolerability. The participants in the OPERA trial will receive UDCA in combination with the trial IMP (OCA or matched placebo). UDCA will be prescribed in line with NHS Standard of Care (usually 13–15 mg/kg daily) and will be prescribed, dispensed and received by the participant, outside of the parameters of this trial. Intolerability to UDCA will be managed as per standard of care. Treatment with UDCA will be recorded as a concomitant medicine.

### Patient identification

Recruiting from 14 centres specialising in the area of PBC management across the UK, participants will be identified at routine clinics or by database search. Sites will use a letter of invitation and Participant Information Sheet to approach patients who are potentially eligible for the trial.

Secondary centres can also identify newly diagnosed PBC patients and, on receiving permission, refer to their local participating site.

Patient awareness will be raised through patient groups, newsletters, websites and social media. The trial will also be highlighted through local and national speaker meetings, production of posters and opportunities to discuss the trial with members of the clinical team.

### Eligibility criteria

The inclusion and exclusion criteria for the trial are described in table 2.

**Table 2 T2:** Eligibility criteria

Inclusion criteria	Established diagnosis of PBC based on the presence of at least 2 out of the 3 key disease characteristics, specifically: Anti-mitochondrial antibody (AMA) or PBC-specific anti-nuclear antibodies (ANA) at a clinically diagnostic level. Elevated ALP (above the upper limit of normal (ULN) for the relevant laboratory). Compatible or diagnostic liver biopsy. Ongoing elevation of ALP (≥15% above ULN) at screening. Disease duration of <6 months from date of diagnosis at the time of consent. Use of UDCA for <3 months at the time of consent. Increased risk of not achieving disease remission with treatment (for the purposes of the trial defined as a pre-treatment ursodeoxycholic acid response score^10^ with a predicted risk of future non-remission of liver biochemistry (ie, ALP>ULN) with UDCA alone of >20%). For people of childbearing potential: an agreement to use at least an acceptable effective method of contraception or to practise sexual abstinence* to avoid pregnancy for the entire duration of the trial period. Willing to complete the trial assessment protocols. Ability to consent, able to comply with trial protocol and attend clinic visits. Age ≥18 years at the time of consent.
Exclusion criteria	Clinical contraindication to obeticholic acid use. Untreated, clinically significant pruritus (patients with effectively treated pruritus are eligible for inclusion). Concomitant use of fibric acid derivatives (eg, bezafibrate or fenofibrate) within 14 days prior to screening. Clinical suspicion of cirrhosis evidenced by a history of one or more of the following: ascites requiring diuretic therapy or percutaneous drainage. endoscopically confirmed varices. liver biopsy suggesting cirrhosis. platelet count <150×10^9^/L. transient elastography score >16.9 kPa within 3 months prior to or at screening. hepatocellular carcinoma confirmed by biopsy or two imaging modalities. hepatic encephalopathy. Bilirubin >twice the ULN other than in the context of Gilbert’s syndrome or another cause of unconjugated hyper-bilirubinaemia. Evidence of complete biliary obstruction. Previous exposure to obeticholic acid (either in clinical trials or in clinical practice) or other potential PBC-modifying therapy. Regular (more than 1 week per month) alcohol consumption in excess of recommended safe limits (14 units per week). Active participation in another interventional trial or exposure to another experimental drug within five half-lives. Pregnancy or planning to get pregnant within the duration of participation in the trial. Currently breastfeeding. Overlapping features of an additional liver disease, including autoimmune hepatitis (using the Paris criteria for autoimmune hepatitis overlap). Hypersensitivity to the active substance or to any of the excipients. If the participant’s treating clinician deems the patient is not suitable to participate in the trial based on other criteria apparent during screening or from medical history. Previous liver transplantation.

* Abstinence is defined as refraining from heterosexual intercourse during the entire trial period. Abstinence is acceptable only as true abstinence: when this is in line with the preferred and usual lifestyle of the patient. Periodic abstinence (eg, calendar, ovulation, symptothermal, post-ovulation methods) and withdrawal are not acceptable methods of contraception.

ALP, alkaline phosphatase; PBC, primary biliary cholangitis; UDCA, ursodeoxycholic acid.

### Consent

Potentially eligible participants will be invited for a screening visit where informed consent will be taken (online supplemental material). Screening will take place in a dedicated session held at the clinic facility in which normal care is offered, or at a research specific visit. Patients will be encouraged to ask questions about the trial and consider whether they wish to participate. The patient will be informed of their right to withdraw from the trial at any time without being subject to any resulting detriment, by revoking their informed consent.

Consent will be obtained prior to any activities undertaken as part of the screening visit (visit 1). Consent for the optional biopsy sub-study will also be obtained at this point if the participant chooses to take part.

### Randomisation

Eligible patients will be randomised to one of two treatment arms, OCA or matched placebo, in a 1:1 ratio. Treatment allocation is double blind, though emergency unblinding is available for medical or safety reasons where it is necessary for the treating clinician to know the participants’ treatment allocation.

The allocation sequence will be computer-generated, using a random permuted block design; blocks might vary in size and will not be disclosed, to ensure concealment. Patients will be randomised in a ratio of 1:1 (placebo: intervention), with stratification according to consent to the biopsy sub-study (to ensure equal allocation between arms in the sub-study).

Randomisation will be carried out using the trial database, Sealed Envelope (London, UK), a central, secure, 24-hour, web-based randomisation system with concealed allocation.

### Participant follow-up assessments

Participants will attend a total of up to five in-person visits and one phone call. These include the screening visit prior to randomisation and baseline visit, (screening and baseline visits may be concurrent if the patient has had recent useable blood results to use for screening), a visit at the end of the treatment phase and a final visit at the end of the follow-up phase. A detailed breakdown of the trial follow-up and assessments required at each visit for OPERA is illustrated in figure 1. The assessments to be conducted are as follows:

Clinical review: Clinical history relevant to PBC and this trial, adapted according to the type of visit. At screening, this will include demographics, a detailed clinical review of PBC and its symptoms as well as medication history. At subsequent visits, this will include any changes in the history since screening, including any symptom changes or de novo symptom development and/or difficulties with taking medication.Clinical examination: A full physical examination will be conducted, including examination of skin; lymph nodes; eyes; ears; nose; throat; respiratory; cardiovascular; abdomen; musculoskeletal; neurological assessment; mental status assessment. Bodyweight will also be measured.Vital signs: Heart rate, blood pressure and temperature will be recorded.Blood sampling: A blood sample will be taken (maximum 50 mL) at times specified in figure 1 for the following assessments:Renal function: urea, creatinine and serum electrolytes.Liver biochemistry: alanine transaminase (ALT), aspartate aminotransferase (AST), alkaline phosphatase (ALP), total bilirubin, direct bilirubin, gamma-glutamyl transferase (GGT), albumin.Cholesterol (total cholesterol, Low Density Lipoprotein (LDL), High Density Lipoprotein (HDL), total:HDL ratio and triglycerides).Full blood count (haemoglobin, platelets and white cells—neutrophils and lymphocytes).Clotting: Prothrombin time and activated partial thromboplastin time.Experimental chemokine blood marker.Optional biobank blood sample.Clinical samples will be analysed in the clinical laboratories of the trial site, following standard local laboratory procedures.All chemokine samples will be analysed simultaneously at the end of the trial. All chemokine assessments will be performed in a fully blinded manner, with regard to treatment group and pre-therapy and post-therapy timing.There are three optional additional blood samples (baseline, visits 4 and 5) for use in future PBC research.Urine sampling: Participants will be asked if they are willing to provide consent to give two optional urine samples (baseline and visit 5).URS: Predicts the likelihood of someone responding to UDCA.^10^ URS must be calculated using the OPERA URS calculator that is provided as part of this clinical trial and available here: https://www.mat.uniroma2.it/~alenardi/URS.html.The URS calculator considers three different ‘cut-offs’ to define UDCA response. In this trial, we use the version that considers the outcome of interest to be biochemical remission (ie, ALP <1× upper limit of normal (ULN)). Based on the URS value, a predicted probability of biochemical remission can be calculated. For the purposes of trial eligibility, URS will be calculated using blood results prior to treatment with UDCA.Pregnancy testing: For people of childbearing potential, a pregnancy test will be carried out during the trial screening visit.EQ-5D-5L: A five-item, validated general quality of life measure from which health utility can be calculated.^26^PBC-40: A disease-specific, patient-derived multidomain quality of life measure. It has six domains relating to fatigue, cognitive symptoms, social function, emotional status and general symptoms.^5^Patient Health Questionnaire: A non-validated 5-point scale to assess health status perceived by participants in response to the trial medication at 26 and 52 weeks.Transient elastography (fibroscan): Clinically validated non-invasive tool used to assess liver stiffness; a surrogate marker of liver fibrosis.Compliance: Compliance regarding IMP will be checked at the interim telephone visit (4 weeks after taking IMP at day 0) and followed up at a clinic visit at week 12 and week 26. IMP compliance will be recorded in the Clinical Data Management System (CDMS). Pharmacy will count and record all returns received from each participant on the IMP accountability log. An accountability check will also be performed as part of on-site monitoring visits.
